### Factors associated with AKI

A key aim of OAKS is to identify perioperative factors that may be associated with subsequent development of AKI. To record this, data will be collected on patient-related, disease-related and pharmaceutical variables (table 1). Detailed description of all data fields is available in the online supplementary file.

**Table 1 BMJOPEN2015009812TB1:** Explanatory data variables collected for OAKS Study

Patient	Disease	Pharmaceutical
Age	Urgency of operation	Perioperative use of NSAIDs
Gender	Underlying pathology	Perioperative use of ACEi or ARBs
Ethnicity	Intraoperative contamination	Perioperative use of diuretics
American Society of Anaesthesiologists (ASA) Score	Baseline haemoglobin and albumin	Postoperative aminoglycosides
History of ischaemic heart disease	Perioperative red cell transfusion	Perioperative use of intravenous contrast
History of congestive heart disease		
History of cerebrovascular disease		
History of hypertension		
History of diabetes		
Smoking status		

ACEi, ACE inhibitors; ARB,angiotensin-receptor blocker; NSAIDs,non-steroidal anti-inflammatory drugs; OAKS, Outcomes After Kidney injury in Surgery.

### Centre questionnaire

Supervising consultants will be asked to complete a short centre questionnaire about the resources available at their centre (table 2).

**Table 2 BMJOPEN2015009812TB2:** Centre questionnaire

Question	Options
(1) Are patients undergoing *elective* major surgery at your centre reviewed at a formal preoperative assessment clinic?	Yes—all patients; Yes—high-risk patients only; No
(2a) Do your centre's U&E (urea and electrolytes) results include AKI stage?	Yes; No
(2b) Does your centre have an electronic alerting system to flag patients that have developed AKI?	Yes; No
(3) Does your centre employ a full-time on-site nephrologist (consultant or associate specialist grade at this hospital)?	Yes; No
(4) Does your centre offer inpatient dialysis?	Dialysis in ICU only (CRRT); Acute dialysis in a renal centre; Both
(5) Is intraoperative goal directed fluid therapy available at your centre for major surgery?	Yes—routinely employed (>50% of cases); Yes—not routinely employed (<50% of cases); No
(6) Are patients undergoing major surgery at your centre admitted to high dependency/intensive care units postoperatively?	Yes—routinely (>50% of patients); Yes—most high-risk patients only; Never

AKI, acute kidney injury; CRRT, continuous renal replacement therapy; ICU, intensive care unit.

### Quality assurance

Each local team of medical students will be supervised by a qualified doctor (ranging from foundation year to registrar grade) and a consultant surgeon.

A detailed protocol for collaborators describing how to register and run the study will be made available online. It will provide a detailed data dictionary, along with guidance on potential data sources for collaborators to use when collecting the data. The protocol will be presented at collaborator meetings across the UK, enabling participants to clarify any uncertainties in person with the steering committee.

Collaborators will be asked to complete mandatory online e-learning modules covering study inclusion criteria, AKI, the Clavien-Dindo classification system and data governance protocols. This will ensure collaborators are able to safely collect accurate data.

To identify any local issues regarding data collection, all participating centres will be asked to pilot patient identification and case record completion for 1 day in the week leading up to the main study starting date. The steering committee will offer support throughout this period to resolve any problems.

### Validation

Only data sets with >95% data completeness will be accepted. Final year medical students or qualified doctors not involved in initial data collection will act as independent assessors, reviewing data collected at a local centre. Overall independent assessors will validate a minimum of 5% of patient records, with a target of >95% case ascertainment and >98% data accuracy.

### Data management

Data will be collected and stored online through a secure server running the Research Electronic Data Capture (REDCap)^18^ web application, hosted at the University of Edinburgh. REDCap is widely used internationally by academic organisations to store research databases. Collaborators will be given secure login details including a password for the REDCap project server. All transmission and storage of web-based information by this system is encrypted. Any patient identifiable information will not be available for data-analysis and will be automatically stripped from the database when exported from REDCap.

### Anticipated minimum recruitment

Based on our previous collaborative studies,^19^ an average centre performs approximately 20 operations meeting the study inclusion criteria in a 14-day period. At most centres in our previous study three data collection teams participated at each centre, collecting data over consecutive 14-day periods. Previously at least four centres participated at each of the 38 medical schools involved. Overall, we estimate that a minimum of 6840 patients will be recruited. The observational nature of the study's primary outcome means a power calculation is not required.

### Statistical analysis

Differences between demographic groups will be tested with the χ^2^ test for categorical data, with differences in continuous data analysed using Student t test. Two-sided statistical significance will be defined at the level of p<0.05. Multivariable binary logistic regression will be used to provide adjusted estimates of effects. Variables to be entered to the model will be those that occur prior to the operation. Initially all these variables will be considered. Variables to remain in the final model will be selected by best using Akaike Information Criterion (AIC). Effect estimates will be presented as ORs and bootstrapped 95% CIs and p values. All relevant second order interactions will be examined. We will explore the possibility of creating a risk prediction model. Such a model would be derived from one half of the data set and validated in the other half. Data handling and analysis will be performed in REDCap and R (R Foundation Statistical Programming, Vienna, Austria).

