**Methods and analysis:**

This prospective, collaborative, multicentre cohort study will include consecutive adults undergoing gastrointestinal resection, liver resection or reversal of ileostomy or colostomy. Open and laparoscopic procedures in elective and emergency patients will be included in the study. The primary end point will be the incidence of AKI within 7 days of surgery, identified using an adaptation of the National Algorithm for Detecting Acute Kidney Injury, which is based on the Kidney Disease Improving Global Outcomes (KDIGO) AKI guidelines. Secondary outcomes will include persistent renal dysfunction at discharge and 1 year postoperatively. The 30-day adverse event rate will be measured using the Clavien-Dindo scale. Data on factors that may predispose to the development of AKI will be collected to identify variables associated with AKI. Based on our previous collaborative studies, a minimum of 114 centres are expected to be recruited, contributing over 6500 patients in total.

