## Background

Studies in cardiac surgery suggest that postoperative acute kidney injury (AKI) is common and strongly associated with increased morbidity, mortality and healthcare costs,^1–3^ but there is less evidence on the incidence and burden of AKI following gastrointestinal and liver surgery. Previous studies have reported the incidence of postoperative AKI after gastrointestinal surgery between 1 and 22%;^4–7^ this broad range reflects both heterogeneity in definitions of AKI and the limitations of retrospective data analysis.

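### The Student t test named for continuous variables keeps its 5% level across groups of very unequal size only if their spread is equal; naming the Welch test removes that condition at no cost

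*Protocol article*

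**What the plan says.** The Statistical analysis section of the protocol article opens with the unadjusted comparisons. "Differences between demographic groups will be tested with the" chi-squared test where the data are categorical, with "differences in continuous data analysed using Student t test". It continues: "Two-sided statistical significance will be defined at the level of p<0.05". It mentions no unequal-variance version of the t test and no check of equal variance.

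Three other places bear on the point:

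- **Group sizes.** Background: "Previous studies have reported the incidence of postoperative AKI after gastrointestinal surgery between 1 and 22" per cent.
- **Sample size.** Anticipated minimum recruitment: "Overall, we estimate that a minimum of 6840 patients will be recruited".
- **Continuous variables.** Table 1, under Factors associated with AKI, lists age and "Baseline haemoglobin and albumin" among the explanatory variables.

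Adjusted estimates come from a different method: multivariable logistic regression, with the model chosen by AIC and bootstrapped confidence intervals and p values.

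**The concern.** Student's t test estimates one common variance from both groups, and the larger group dominates that estimate. If the smaller group is more variable, the pooled standard error is too small and p values come out too low. If the smaller group is less variable, the opposite happens. With groups of equal size the two effects cancel in large samples; with a small minority group they do not.

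A cohort of several thousand might seem to make the choice of t test immaterial. Size does protect against skewed data. It does not protect against unequal spread combined with unequal group sizes. At stake is whether the declared 5% threshold means 5% in the unadjusted table of continuous variables.

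**Working it through.** **Inputs**

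- Nominal level: 0.05, two-sided (Statistical analysis).
- AKI share *p*: 1 to 22% (Background), a split of about 1:99 to 1:3.5.
- Total *N*: 6840 (Anticipated minimum recruitment). At shares of 1%, 10% and 22% the AKI group would have 68, 684 and 1505 patients.
- SD ratio *r*, AKI over non-AKI: **not in the document**. Assumed range 0.8 to 1.5, with 1.0 as reference.
- Grouping by AKI status: **inferred**, as explained under the objection.

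**Formula**

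Let the non-AKI standard deviation be 1, n1 = pN and n2 = (1−p)N.

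- True variance of the difference in means: r²/n1 + 1/n2 = [(1−p)r² + p] / [N p(1−p)].
- Variance the pooled test uses, in large samples: [p r² + (1−p)] × (1/n1 + 1/n2) = [p r² + (1−p)] / [N p(1−p)].
- Their ratio: R = [(1−p)r² + p] / [p r² + (1−p)]. *N* cancels.
- Actual level = 2 × [1 − Φ(1.96/√R)].

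**The plan's own figure**

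At r = 1, R = 1 for every *p*, so the stated 5% is reproduced. At p = 0.5, R = 1 for every *r*, so groups of equal size would also be safe.

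**Worked examples at 10% AKI**

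- r = 1.25: R = (0.9 × 1.5625 + 0.1) / (0.1 × 1.5625 + 0.9) = 1.50625/1.05625 = 1.426. √R = 1.194, 1.96/1.194 = 1.641, level = 10.1%.
- r = 0.8: R = (0.9 × 0.64 + 0.1) / (0.1 × 0.64 + 0.9) = 0.676/0.964 = 0.701. √R = 0.837, 1.96/0.837 = 2.341, level = 1.9%.

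**Actual level of the nominal 5% pooled test**

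| AKI share | r = 0.8 | r = 1.0 | r = 1.1 | r = 1.25 | r = 1.5 |
|---|---|---|---|---|---|
| 1% | 1.5% | 5.0% | 7.4% | 11.5% | 18.7% |
| 10% | 1.9% | 5.0% | 6.9% | 10.1% | 15.4% |
| 22% | 2.7% | 5.0% | 6.3% | 8.3% | 11.5% |
| 50% (reference) | 5.0% | 5.0% | 5.0% | 5.0% | 5.0% |

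**Simulation check**

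Normal data with equal means, 100,000 runs per setting. At 10% AKI and r = 1.25 the pooled test rejected in 9.99%, 10.07% and 10.15% of runs at N = 684, 6840 and 68,400, so the error does not shrink as the sample grows. The Welch test rejected in 4.9 to 5.1% of runs in every setting tried (the same three values of *N*; shares of 1%, 10% and 22%; SD ratios from 0.8 to 1.5).

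**The case against.** The case on the other side is substantial, and most of it stands as a limit on the point.

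- **The groups are not named as AKI and non-AKI.** The section speaks only of demographic groups. AKI status is an inference: the listed outcomes are incidences, rates or yes/no states, the continuous items in Table 1 are explanatory variables, and a secondary aim is to find variables associated with AKI. If the groups compared were of about equal size, the problem would disappear.
- **No standard deviations are given.** A reader might infer that the p values will be wrong. The document does not support that. With equal spread there is no error, and nothing in the article shows whether AKI patients are more variable, less variable or the same.
- **No main result uses this test.** A reader might also infer that the AKI risk-factor findings are compromised. They are not. The primary outcome is an incidence, the secondary outcomes are proportions or rates, and the adjusted odds ratios come from logistic regression. Entry to that model is not screened by t test, since all preoperative variables are considered first and AIC then selects. The article also describes the study as one that generates hypotheses.
- **The wording may be loose.** Student t test is often used as a generic label, and the plan names R, whose t.test function runs the Welch version by default. The analysts may therefore run the better test anyway. But the text as written names the equal-variance test, and someone following it literally would override that default.

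What remains is narrow: the plan names a test that carries an assumption it neither needs nor supports.

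**Conclusion.** The point holds as a minor, conditional one. If the continuous variables are compared by AKI status, the named test meets its 5% level only under equal spread. For SD ratios of 1.1 to 1.25 and AKI shares of 1 to 22%, the actual level would be 6.3 to 11.5%; at a ratio of 0.8 it would be 1.5 to 2.7%. These figures rest on the inferred grouping and on assumed SD ratios, and they do not depend on the sample size. The consequence is confined to unadjusted p values for a few continuous variables. This is a free improvement to the wording, not a fault that threatens a stated conclusion of the study.

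**What to change.** In the Statistical analysis section, replace Student t test with Welch (unequal-variance) t test. It would help to state in the same sentence which groups are compared, for example patients with and without AKI within 7 days. The change needs no new data and no additional patients, and the loss of power at about 6840 patients is negligible.

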## Methods

### Study design

A multicentre prospective cohort study disseminated through collaborative medical student networks (figure 1).

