### Study setting

Hospitals in the UK and the Republic of Ireland that offer elective or emergency gastrointestinal or liver surgery will be invited to participate. Each centre may contribute up to four, 2-week sets of consecutive patient data.

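### The stated analysis makes no provision for centre: intervals for AKI incidence, and tests of factors that differ between centres, would be too optimistic if it is followed as written

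*Protocol article*

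**What the plan says.** Study design describes "A multicentre prospective cohort study disseminated through collaborative medical student networks". The Abstract expects that "a minimum of 114 centres are expected to be recruited, contributing over 6500 patients in total". Anticipated minimum recruitment gives the size of each cluster: "an average centre performs approximately 20 operations meeting the study inclusion criteria in a 14-day period", and at most centres in the previous study "three data collection teams participated at each centre, collecting data over consecutive 14-day periods". Study setting allows more: "Each centre may contribute up to four, 2-week sets of consecutive patient data".

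Statistical analysis compares groups with chi-squared and Student t tests at a two-sided 5% level. It then states: "Multivariable binary logistic regression will be used to provide adjusted estimates of effects". Variables are selected by AIC, and "Effect estimates will be presented as ORs and bootstrapped 95% CIs and p values". It names no centre term, random effect, GEE, cluster-robust error or resampling by centre, and no other section does so.

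Centre-level information is nonetheless collected: "Supervising consultants will be asked to complete a short centre questionnaire about the resources available at their centre". The Discussion gives the wide differences in fluid management between UK centres as the reason for not recording fluid therapy, which the article elsewhere treats as a possible contributor to AKI.

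**The concern.** Chi-squared tests, t tests and ordinary logistic regression treat patients as independent. Patients from one hospital share case mix, perioperative care, a data-collecting team and blood-testing habits. Testing habits matter because no extra blood tests are done for the study, so whether AKI is detected depends partly on local practice. The article also leaves a centre-varying possible cause of AKI, fluid therapy, unmeasured by design.

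The primary aim is at stake: an incidence meant for benchmarking and for designing later trials. So is the claim that particular factors are associated with AKI, wherever those factors differ between hospitals.

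**Working it through.** **Inputs from the article.** About 20 eligible operations per centre per 14 days; typically 3 periods (maximum 4); at least 114 centres (Abstract); minimum N = 6840; earlier reports of incidence from 1% to 22% (Background); two-sided 5% level.

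**Assumed inputs.** The article gives no ICC, so 0.01, 0.02 and 0.05 are used on the observed (0/1) scale. Incidence is taken as 10%, within the cited range.

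**The plan's own figure.** 20 × 3 = 60 patients per centre, and 114 × 60 = 6840, which reproduces the stated minimum. The recruitment section's own inputs, 4 centres × 38 schools = 152 centres, would give 152 × 60 = 9120. That mismatch is a separate matter. The design effect below depends on patients per centre, not on the number of centres.

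**AKI incidence.** Design effect DE = 1 + (60 − 1) × ICC. Effective N = 6840 / DE. Half-width = 1.96 × √(0.10 × 0.90 / 6840 × DE). Coverage of an interval that ignores centre = 2Φ(1.96 / √DE) − 1.

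| ICC | DE | Effective N | True half-width (points) | Coverage of nominal 95% |
|---|---|---|---|---|
| 0 | 1.00 | 6840 | 0.71 | 95% |
| 0.01 | 1.59 | 4302 | 0.90 | 88% |
| 0.02 | 2.18 | 3138 | 1.05 | 82% |
| 0.05 | 3.95 | 1732 | 1.41 | 68% |

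At 22% incidence the half-width goes from 0.98 to 1.24, 1.45 and 1.95 points. At 1% it goes from 0.24 to 0.30, 0.35 and 0.47. With four periods (80 per centre) the design effects become 1.79, 2.58 and 4.95.

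**Centre-level factors, by formula.** The true size of a nominal 5% test is 2 × (1 − Φ(1.96 / √DE)), which gives 12%, 18% and 32% at ICC 0.01, 0.02 and 0.05.

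**Factors by simulation.** 114 centres × 60 patients, AKI about 10%, a binary factor with no true effect, an unadjusted odds ratio with the usual standard error and no centre term, and 4000 runs per setting. Cells show the type I error and, in brackets, the true standard error divided by the one reported. Columns give the share of the factor's latent variance that lies between centres.

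| Latent ICC of AKI | 0 | 0.1 | 0.3 | 1 (centre-level) |
|---|---|---|---|---|
| 0.02 | 5.5% (1.01) | 5.0% (1.00) | 5.3% (1.02) | 9.5% (1.17) |
| 0.05 | 5.2% (1.00) | 6.2% (1.03) | 7.0% (1.08) | 16.2% (1.41) |
| 0.10 | 4.6% (0.98) | 6.3% (1.06) | 10.3% (1.21) | 26.1% (1.75) |

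The simulation sets the ICC on the latent logistic scale. At 10% incidence, latent values of 0.02, 0.05 and 0.10 correspond to about 0.006, 0.016 and 0.033 on the observed scale. The formula then gives about 9%, 16% and 25%, in agreement with the last column.

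**The case against.** The strongest reply is that this is one paragraph of a condensed article and that parts of the criticism go beyond its text. Several stronger readings are tempting but not supported:

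- **That the bootstrap ignores centre.** The resampling unit is not stated. Resampling whole centres would fit the same sentence.
- **That the incidence will carry a falsely tight interval.** No interval method for incidence is given; the bootstrapped intervals are for odds ratios. The 0.71 points is what the usual binomial formula would yield, not a figure from the article.
- **That questionnaire variables will be tested with a badly inflated error rate.** No section says they will be related to AKI, and Table 1 lists only patient, disease and pharmaceutical variables.
- **That all intervals and p values are wrong.** The simulation shows nil to modest harm for patient-level factors, which are the ones Table 1 lists.
- **That centre confounds the odds ratios and a random intercept or GEE would cure it.** Neither alone removes confounding by centre. That needs fixed centre effects or separate within- and between-centre terms.

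The upper ICC is also demanding. At 10% incidence, 0.05 implies a between-centre standard deviation of √(0.05 × 0.09) = 6.7 percentage points, and no section supports that. At 0.01 it is √(0.01 × 0.09) = 3.0 points, and the loss of precision (0.71 to 0.90) is small against the cited 1% to 22%. The article calls the study hypothesis generating, and no sample size or decision rule depends on these standard errors.

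These points limit the reach of the concern but do not remove it. The section is specific about tests, model class, selection criterion and interval method. What it names assumes independent patients, in a study whose own text says that centres differ. An unseen analysis plan may deal with centre, but the published text would still need to agree with it.

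**Conclusion.** The point holds in a limited form: the analysis as published makes no provision for centre. How much this matters depends on the quantity estimated:

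- **AKI incidence:** an interval that ignores centre understates the standard error by a factor of 1.26 to 1.99 at ICC 0.01 to 0.05 with 60 patients per centre.
- **Any centre-level factor that is analysed:** true test size 12% to 32% over the same ICC range, against a nominal 5%.
- **Patient-level factors that vary between centres:** modest effect, with simulated type I error of 5.0% to 10.3%.
- **Patient-level factors that do not vary between centres:** essentially unaffected (4.6% to 5.5%).

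The direction is firm, but the sizes are ranges: they rest on assumed ICCs, an assumed 10% incidence and equal centre sizes. The simulation covers unadjusted odds ratios only.

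**What to change.** In Statistical analysis:

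1. Specify a mixed-effects logistic model with a random intercept for centre. It keeps a likelihood, so the planned AIC selection still works; GEE has none and would not fit that step.
2. State that the bootstrap resamples whole centres.
3. Give the AKI incidence a cluster-robust confidence interval.
4. Report the between-centre variance, which is also useful for designing later trials.
5. If questionnaire variables are analysed, do so only in a model with centre as a level.

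The cost is somewhat wider intervals and slightly more analysis work. Odds ratios from this model are conditional on centre, and the text should say so. No new data are needed: linking each centre's questionnaire to its patients already requires a centre identifier, although the article does not list one.

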## Ethics and dissemination

### Research ethics approval

OAKS is a clinical audit based on National Institute for Health and Clinical Excellence (NICE) Clinical Guidelines requiring preoperative and postoperative measurement of serum creatinine in all patients undergoing major surgery.^20–22^ The South East Scotland Research Ethics Service advised that ethical approval is not required for OAKS in the UK. Participating centres will register OAKS locally as a clinical audit. They will also ensure they have successfully applied for Caldicott Guardian approval to submit anonymised patient data to a national audit and secure online database. In the Republic of Ireland collaborators are responsible for securing approval for the study from their local research ethics service.

